### Procedure for unblinding if needed {17b}

Not applicable. There is no blinding.

## Data collection and management

### Plans for assessment and collection of outcomes {18a}

Written protocol (in paper) provides systematic measurements that assessor has to collect. All assessors will attend compulsory training how to carry out every step in the study. All study-related documents are on cloud that can be accessed by study personnel.

### Plans to promote participant retention and complete follow-up {18b}

Participants are studied only up to 5 days or discharge from the hospital, whichever comes first. The study doesn’t require any extra actions or active collaboration from patients. If the patient deviates from intervention protocols, we will use data of the patient up to the timepoint of deviation if eligible; if not, the patient will be excluded. Exclusion probability is low due to the short period of observation and low to none patient active collaboration.

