## Interventions

### Explanation for the choice of comparators {6b}

Classic palpation approach for vascular access is challenging in DIVA patients. Up to 50% of orthopedic patients are DIVA [1, 2] and orthopedic surgeries are on the rise in developed countries. Medical staff can site venous cannula only to veins they can see. Therefore, the cannula is often in a suboptimal place of flexion of the arm in the wrist or elbow which are associated with complications [6, 7] and higher failure rates up to 63% [8].

Ultrasound enables us to place the cannula in an ideal place, in terms of the complications mentioned above. In addition, we can measure the diameter of the vein and use cannula width that will obscure only one third of the internal lumen. This should allow for blood draw because of undisturbed bloodstream in the vein.

We chose the UGVA approach in comparison to the classic palpation approach in standard clinical settings. This design of study allows to compare the standard of care (insertion of cannula by palpation) to the modern (ultrasound-guided insertion of cannula), technically more challenging but also a more rewarding option.

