## Statistical methods

### Statistical methods for primary and secondary outcomes {20a}

The primary and secondary outcomes will be evaluated using the *χ*^2^ test in terms of the difference in approaches of cannula insertion between groups in the number of punctures and the failure rate of the cannulas (failure rate is defined as the proportion of cannulas requiring reinsertion within 5 days after insertion). RR and 95% confidence interval of successful venous cannulation will be also calculated. The primary endpoint is the number of attempts to successful cannulation determined by the number of skin punctures. More attempts are associated with complications. As a secondary endpoint, the failure rate is calculated from the ratio of cannulas that did not fail to cannulas that failed for any reason in each group, up to the first 5 days postoperatively. This data is obtained from the patient protocol (Fig. 2). Primary and secondary outcomes will be reported as frequencies and percentages. For our tertiary outcome, to compare differences between the intervention groups (time required for cannula insertion, number of cannulas used, A-DIVA scoring system, etc.), *t*-test for independent groups or Mann–Whitney U test will be used, if data are not normally distributed. The effect of the intervention on outcome variables will be determined by using paired *t*-test or Wilcoxon signed-rank test for data obtained at baseline and for 5 days of the study. Other endpoints include portion of long PVCs that are able to ensure blood draw up to 5 days postoperatively, time needed to insert PVC in each group, reinsertion of PVC needed in both groups for any reason. All this data is recorded in the study protocol.

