### Methods in analysis to handle protocol non-adherence and any statistical methods to handle missing data {20c}

Not all processes set up in the study deviate from the design of the randomized controlled clinical trial. When analyzing data, if any qualitative or metric data is found, we will first contact a team member who records or measures the data to supplement the missing data, if at all possible, while analyzing the reasons why the data is missing. We will use all available SPSS applications to check/analyze data completeness. In addition, SPSS statistical programs can evaluate and process incomplete data sets correctly (each analysis uses only cases without missing values for all variables and for all analyses). Therefore, we will not artificially attribute any missing values and we will take into account the missing data in the interpretation of the results. Patients with a large amount of missing data will be excluded from the final statistical analysis.

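### Secondary endpoint: observation stops at discharge, but cannula failure is analysed as a fixed 5-day proportion, with no rule for patients who leave event-free before day 5

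*Protocol article*

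**What the plan says.** All references are to the protocol article.

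- **Follow-up {18b}:** "Participants are studied only up to 5 days or discharge from the hospital, whichever comes first". Observation time therefore varies between patients.
- **Endpoint definition {20a}:** "failure rate is defined as the proportion of cannulas requiring reinsertion within 5 days after insertion". The window is a fixed 5 days.
- **Calculation {20a}:** "the failure rate is calculated from the ratio of cannulas that did not fail to cannulas that failed for any reason in each group". Each cannula is sorted into failed or not failed, and time under observation plays no part.
- **Test and reporting {20a}:** a chi-square test for the difference "between groups in the number of punctures and the failure rate of the cannulas", and "Primary and secondary outcomes will be reported as frequencies and percentages".
- **Missing data {20c}:** no imputation, and "each analysis uses only cases without missing values for all variables and for all analyses". Discharge before day 5 is not mentioned.
- **Deviations {18b}:** for a patient who departs from the intervention protocol, "we will use data of the patient up to the timepoint of deviation if eligible; if not, the patient will be excluded". This rule covers deviations, not ordinary discharge, and it names no method for the shortened follow-up.

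The article gives no minimum stay, contact after discharge, censoring rule or time-to-event method.

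**The concern.** A proportion over a fixed 5-day window is well defined only if every cannula is followed for 5 days or until it fails. Under {18b} that is not guaranteed. A cannula still working when the patient leaves on day 3 has shown 3 days of service and nothing about days 4 and 5. A failed/not-failed table must either put it beside a cannula that worked for 5 days or leave it out.

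What is at stake is the trial's durability claim. The Outcomes section {12} aims to compare how long the inserted cannulas serve, and the Background {6a} presents patency up to 5 days as the novelty. If length of stay enters the failure rate, the reported percentages are not 5-day failure rates and cannot be compared with other 5-day figures.

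**Working it through.** **Inputs.** The article gives no length of stay and no design failure rate for this endpoint. The only related figure is the background statement in {6b} of "higher failure rates up to 63"%, for cannulas at unfavourable sites. There is thus no planned figure to reproduce. Everything below is an assumption: true 5-day failure *p* of 40% (control) and 25% (ultrasound), constant hazard over the 5 days, and a share *q* of each arm discharged on day 3, with the rest observed to day 5.

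**Failure by day 3.** F(3) = 1 − (1 − p)^(3/5).
- Control: 1 − 0.60^0.6 = 0.264
- Ultrasound: 1 − 0.75^0.6 = 0.159

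**Reading A: early event-free discharges count as not failed.** Crude proportion = q × F(3) + (1 − q) × p.

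| Share leaving on day 3 | Control | Ultrasound | Difference | Risk ratio |
|---|---|---|---|---|
| 0% (truth) | 40.0% | 25.0% | 15.0 points | 0.625 |
| 10% | 38.6% | 24.1% | 14.6 points | 0.623 |
| 25% | 36.6% | 22.7% | 13.9 points | 0.621 |
| 50% | 33.2% | 20.4% | 12.8 points | 0.615 |
| 100% | 26.4% | 15.9% | 10.5 points | 0.601 |

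For the 50% row, control is 0.5 × 0.264 + 0.5 × 0.40 = 0.332 and ultrasound is 0.5 × 0.159 + 0.5 × 0.25 = 0.204.

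**Reading B: early event-free discharges are dropped as incomplete.** All observed failures stay in, but only cannulas working to day 5 remain as successes. Proportion = crude / [crude + (1 − q)(1 − p)]. With q = 50%:
- Control: 0.332 / (0.332 + 0.5 × 0.60) = 0.332 / 0.632 = 52.5%
- Ultrasound: 0.204 / (0.204 + 0.5 × 0.75) = 0.204 / 0.579 = 35.3%

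The same data thus give 33.2% vs 20.4% or 52.5% vs 35.3%, on either side of the true 40% vs 25%.

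**Does it create a false difference?** With equal durability and the same discharge timing in both arms, the two crude rates are equal, so no. If timing differs, with 20% of one arm and 60% of the other leaving on day 3, a difference appears where there is none:
- p = 20% in both arms: 18.5% vs 15.5%, 3.0 points
- p = 40% in both arms: 37.3% vs 31.8%, 5.4 points
- p = 63% in both arms: 59.4% vs 52.2%, 7.2 points

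**Would a competing-event analysis help?** If every patient is followed to failure, to discharge or removal, or to day 5, nobody is censored earlier. The day-5 cumulative incidence of failure with discharge and removal as competing events is then failures divided by all cannulas, which is the crude proportion again.

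**The case against.** The strongest reply is that failure during the hospital stay, up to day 5, is a legitimate pragmatic endpoint. A cannula that served until the patient went home did its job and needed no replacement. On that reading the crude proportion is exactly right. The Objectives {7}, framed as the ability to give intravenous therapy up to 5 days after surgery, allow it. This stands as a possible estimand, and the crude figure deserves a place under that name. It does not settle the matter, because {20a} fixes the window at 5 days after insertion and {12} sets out to compare service life.

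Three further limits also stand.

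- A reader might infer that the plan counts early-discharged patients as 5-day successes. The calculation in {20a} points that way, but no sentence says so, and the complete-case wording in {20c} leaves exclusion open.
- A reader might also infer a biased treatment comparison. With similar discharge timing by arm the risk ratio is nearly unchanged and no false effect arises. One arm leaving entirely on day 3 and the other on day 4 would give 26.4% vs 33.5% under equal durability (p = 40%), a gap of about 7 points. Nothing in the article suggests that the cannulation method shifts stay by a whole day in a single-centre randomised trial of the same elective surgery.
- The Participant timeline {13} schedules secondary-outcome assessment on days 2–4 and on day 5. This hints, without proving it, that many patients are expected to be in hospital until then.

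**Conclusion.** The follow-up rule and the endpoint definition do not fit each other. Neither available way of handling an event-free early discharge yields a 5-day failure rate, and the article does not choose between them.

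The harm falls mainly on the absolute rates and the risk difference. In the 40% vs 25% illustration with half leaving on day 3, the crude rates are about 7 and 5 points too low and the difference loses about 2 points. With 10% leaving on day 3 the rates are off by only about 1 point. These figures rest on assumed failure rates, constant hazard and assumed lengths of stay.

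The documents do not support a claim that the comparison is spurious or that the trial's main result is affected. The number of attempts is settled at insertion, and the sample size does not rest on the failure endpoint. This should be corrected before analysis, but it is a secondary-endpoint point only.

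**What to change.** Make the main secondary analysis time from insertion to cannula failure, censored at discharge, removal without failure, or day 5, whichever comes first. Report Kaplan-Meier failure at day 5 per arm with numbers at risk, a log-rank test, and a Cox hazard ratio with 95% CI. State the assumption that discharge and removal are non-informative about later failure.

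Report the crude proportion alongside, labelled as in-hospital failure up to day 5, with all randomised cannulas in the denominator, so that event-free early discharges are not dropped. Do not offer cumulative incidence with discharge as a competing event as the remedy, since it returns the crude proportion.

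Record the day of failure, removal or discharge if the case form (Fig. 2, not shown) does not already do so. Forms are gathered daily {19}, which should make this easy.

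The cost is slightly more analysis work and reliance on the censoring assumption. The gain is an interpretable 5-day rate. It is not extra power, because failures after discharge remain unseen under any method. If very few patients are still under observation on day 5, the day-5 estimate will be imprecise and should be presented as such.

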### Data management {19}

All data is recorded on paper (study protocol) and stored in the anesthetic office in a study case file with limited access. Every day will researchers collect these protocols. Study protocols are then entered into a spreadsheet using Excel (Microsoft Office, 2021, Washington, USA). Double data entry technique will be used with two different researchers or in two different sessions by a single researcher if second is not available. These databases are compared by “IF command in Excel spreadsheet algorithms. After data validity analysis are spreadsheets ready for statistical analysis using SPSS software and Microsoft Excel software.

### Confidentiality {27}

Every patient will get a numerical code instead of his real name on enrolment. Only these codes will be used throughout the study. All emails exchanged between researchers including patients or study data have to use hospital servers only. In addition, every file will be password protected. Hospital standards for data management will be used. During assessors training, there will be time allocated for data management.

### Plans for collection, laboratory evaluation, and storage of biological specimens for genetic or molecular analysis in this trial/future use {33}

Not applicable. No samples were collected.

## Statistical methods

### Statistical methods for primary and secondary outcomes {20a}

The primary and secondary outcomes will be evaluated using the *χ*^2^ test in terms of the difference in approaches of cannula insertion between groups in the number of punctures and the failure rate of the cannulas (failure rate is defined as the proportion of cannulas requiring reinsertion within 5 days after insertion). RR and 95% confidence interval of successful venous cannulation will be also calculated. The primary endpoint is the number of attempts to successful cannulation determined by the number of skin punctures. More attempts are associated with complications. As a secondary endpoint, the failure rate is calculated from the ratio of cannulas that did not fail to cannulas that failed for any reason in each group, up to the first 5 days postoperatively. This data is obtained from the patient protocol (Fig. 2). Primary and secondary outcomes will be reported as frequencies and percentages. For our tertiary outcome, to compare differences between the intervention groups (time required for cannula insertion, number of cannulas used, A-DIVA scoring system, etc.), *t*-test for independent groups or Mann–Whitney U test will be used, if data are not normally distributed. The effect of the intervention on outcome variables will be determined by using paired *t*-test or Wilcoxon signed-rank test for data obtained at baseline and for 5 days of the study. Other endpoints include portion of long PVCs that are able to ensure blood draw up to 5 days postoperatively, time needed to insert PVC in each group, reinsertion of PVC needed in both groups for any reason. All this data is recorded in the study protocol.

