### Criteria for discontinuing or modifying allocated interventions {11b}

The procedure may be performed with or without a tourniquet following the insertion manual (Fig. 1). The method should be discontinued after two unsuccessful attempts and another experienced practitioner should be sought. If such a practitioner is not available it has to be marked in the protocol as “failure” with a note “no experienced practitioner available.” Another researcher makes notes into the study protocol (Fig. 2).

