### Sample size {14}

The estimate for the final sample size was based on the expected drop-out rate and the objective and design of the study. This trial assumes a comparison of the effect on outcome variables in peripheral vein insertion in the USG group and palpation-inserted peripheral venous cannula as the control group. In overall, we hypothesize that it will take fewer attempts to insert the cannula into a vein with the USG technique (USG: 1 vs. C: 1–3), corresponding to a reduction in time of ≥ 3 min (clinically relevant indicator) for successful cannulation in the USG group. When calculating the sample size, based on our experience and literature data, we assumed a 20% risk of complications inserting the cannula into a vein in the standard way, 5% as a probability of a Type I error (α < 0.05), and the power of the test 90% (β = 0.10). Theoretically, we also accepted a 5% risk failure of a first insertion of a cannula into a vein in the USG group. The sample size calculation was based on the result of the risk ratio (RR) between groups as % of complications (unsuccessful prick) with cannula insertion into the peripheral veins [9]. The adequate sample size of 162 patients was calculated as described previously [10], increased by 20% for the case unforeseeable circumstances (technical error, data loss, poor patient cooperation, etc.) and rounded ≅ 200.

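### The trial is sized on failure of the first prick, but the primary test is a chi-square on a puncture count with no stated categories and no value for failed patients

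*Protocol article*

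**What the plan says.** - **Sample size {14}.** The calculation is "based on the result of the risk ratio (RR) between groups as % of complications (unsuccessful prick"). The inputs are, for control, "we assumed a 20% risk of complications inserting the cannula into a vein in the standard way" and, for ultrasound, "we also accepted a 5% risk failure of a first insertion of a cannula into a vein in the USG group". Error rates are given as "5% as a probability of a Type I error (α < 0.05), and the power of the test 90% (β = 0.10"). The section also expects one attempt with ultrasound against one to three in controls, without a distribution.
- **Statistical methods for primary and secondary outcomes {20a}.** "The primary endpoint is the number of attempts to successful cannulation determined by the number of skin punctures". A chi-square test is to compare the groups "in terms of the difference in approaches of cannula insertion between groups in the number of punctures and the failure rate of the cannulas". A risk ratio (RR) with 95% confidence interval for successful venous cannulation is added. Mann–Whitney is named for tertiary outcomes only.
- **Criteria for discontinuing or modifying allocated interventions {11b}.** "The method should be discontinued after two unsuccessful attempts and another experienced practitioner should be sought". If nobody is available, the patient is recorded as a failure.
- **Handling of non-adherence and missing data {20c}.** Only cases without missing values are analysed, and nothing is imputed.

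**The concern.** The quantity that was powered and the quantity that will be tested are not shown to be the same. First-prick failure is a 2×2 comparison. A puncture count compared by chi-square may be a 2×2, 2×3 or larger table, and the protocol does not say which. The trial is unblinded, so a cut-point left open could be chosen with the results in view.

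The second problem needs no simulation. A patient who is never cannulated within the trial procedure has no number of punctures to success. These are the worst outcomes on the primary endpoint, and whether a patient joins them depends partly on whether a second practitioner was free. The discontinuation section does not say whether the second practitioner's punctures are added to the count.

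At stake are the planned power, the interpretation of the reported RR, and whether the comparison is quietly restricted to patients in whom cannulation succeeded.

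**Working it through.** **1. The plan's own figure.** Inputs from Sample size {14}: p1 = 0.20, p2 = 0.05, α = 0.05, power 90%. Equal allocation is assumed. With p̄ = 0.125 and q̄ = 0.875, the total is

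N = 2 × [z(α)·√(2p̄q̄) + z(0.90)·√(p1q1 + p2q2)]² / (p1 − p2)².

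- One-sided α: 2 × (1.645 × 0.4677 + 1.2816 × 0.4555)² / 0.0225 = 2 × (0.7693 + 0.5838)² / 0.0225 = 162.7. This matches the stated 162.
- Two-sided α: 2 × (0.9167 + 0.5838)² / 0.0225 = 200.1.

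The stated 162 is therefore a two-proportion calculation on a binary outcome. By the same formula, 200 analysed patients give about 90% two-sided power for that outcome. That 162 needs a one-sided α is a separate matter.

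**2. Power of the test if it is run on puncture categories.** Simulation with 40,000 trials per row, 100 per arm, two-sided 0.05. First-puncture success is fixed at the protocol's 80% and 95%. The split beyond the first puncture is assumed, because the document gives none.

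| Control split (%) | Ultrasound split (%) | Chi-square on categories | Binary, first puncture | Mann–Whitney |
|---|---|---|---|---|
| 80/12/5/3 | 95/4/0.7/0.3 | 81% | 92% | 93% |
| 80/15/5 | 95/4/1 | 86% | 92% | 92% |
| 80/12/8 | 95/4/1 | 88% | 92% | 92% |
| 80/10/10 | 95/4/1 | 90% | 92% | 93% |
| 80/15/5 | 95/5/0 | 91% | 92% | 93% |
| 80/12/8 | 95/5/0 | 96% | 92% | 93% |
| 80/10/10 | 95/5/0 | 98% | 92% | 94% |

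The binary test gives about 92% in every row because it uses only the figures the protocol states. The multi-category test moves by 17 points on figures the protocol does not state. Its result depends mainly on the number of categories and on how often ultrasound needs a third puncture.

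**3. The risk ratio.** Planned: 0.05 / 0.20 = 0.25, for failure. If the reported RR means first-puncture success, the same inputs give 0.95 / 0.80 = 1.19. If it means success overall, the protocol gives no expected value. Neither is the ratio used for planning.

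**4. Patients recorded as failures.** The open options lead to different analyses:
- Coded as 2: the patient shares a cell with those cannulated on the second puncture, and in a rank test looks better than one who succeeded on the third.
- Left blank: the complete-case rule removes the patient. As an illustration, assume 80/15/5 against 95/4/1 and let the whole third cell be recorded as failures. First-puncture failure among those remaining is 15/95 = 15.8% against 4/99 = 4.0%. The difference shrinks from 15.0 to 11.7 points. The true number of such patients is unknown.
- Given a category of their own: possible, but not stated.

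**The case against.** The strongest reply is that a chi-square test paired with an RR suggests a 2×2 table. If both are read as first-puncture success or failure, the statistical methods agree with the sample size. That reading is reasonable and may be what was meant, but it is not written. The endpoint is described as a count, and the sample size section itself expects one to three attempts in controls.

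A reader might infer that the planned test loses power. The documents do not support that as a general statement. They do not say the count is analysed in unordered categories, and they give no attempt distribution. Some equally plausible splits erase the loss or turn it into a gain. The four-category row also goes beyond the one-to-three range stated for controls.

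A reader might also infer that the RR concerns eventual success, or that it is the primary effect measure. The text says neither. It is an additional calculation and is ambiguous.

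Sparse cells are not a serious objection to the test. Null simulations of the multi-category chi-square at 81 and 100 per arm gave a type I error of 2.9–4.8%, so it is conservative at worst.

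Finally, coding failed patients could be left to an analysis plan, and the failure label is prescribed only where no second practitioner is available. This limits how many patients are affected. It does not repair an endpoint whose definition excludes them, combined with a rule that drops missing values.

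**Conclusion.** The point holds as a misalignment that should be fixed. It is not a proven loss of power. Three things rest on the text alone: the powered outcome is binary while the primary endpoint is a count with no cut-point or ordinal method; the count is undefined for patients recorded as failures; and the RR to be reported is not the 0.25 used in planning.

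The size of the power effect is conditional. If three or four puncture categories are used with 100 analysed per arm, power lies between about 81% and 98%, against about 92% for the binary test and 92–94% for Mann–Whitney. This assumes equal allocation, a two-sided 5% level, the protocol's 20% and 5%, and the splits listed in the table.

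**What to change.** Align the discontinuation, sample size and statistical methods sections before the first patient is randomised, by one of two routes:

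- **(a)** Test first-puncture failure (yes/no) in all randomised patients with the Pearson chi-square. Report the RR of first-puncture failure and the risk difference, each with a 95% confidence interval. Analyse the puncture count as support, by a rank or ordinal method. This is the quantity that was powered.
- **(b)** Keep the count as primary and test it with Mann–Whitney or a proportional-odds model.

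Under either route:
- count the punctures made by all practitioners;
- keep patients recorded as failures in the analysis, as non-success in the binary analysis and at the worst rank in the count;
- state that the RR refers to the outcome of the first puncture.

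The cost is a change of wording and a registry update. Attempts are already recorded, so no new data are needed. Route (a) changes the declared primary endpoint, which route (b) avoids.

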**Methods:**

This investigator-initiated prospective randomized monocentric controlled trial is designed to randomly allocate 200 patients undergoing elective primary total joint arthroplasty of hip or knee to one of two groups as follows: Group C (control group) – peripheral venous cannula insertion by palpation or Group USG (intervention) – cannula insertion by ultrasound-guided vascular access. Our primary endpoint is to compare the number of attempts for ultrasound-guided insertion of the peripheral venous cannula with common palpation insertion of the peripheral venous cannula in overweight/obese patients (BMI ≥ 25). The secondary endpoint is a failure rate of the peripheral venous cannula to administer intravenous therapy up to 5 days postoperatively. Tertiary endpoints include a portion of long PVCs that are able to ensure blood draw up to 5 days postoperatively, time needed to insert PVC in each group, number of needle tip redirections in both groups, and reinsertion of PVC needed in both groups for any reason.

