### Objectives {7}

The primary objective of this investigator-initiated prospective randomized controlled trial is to compare the number of attempts for ultrasound-guided insertion of PVC with common palpation insertion of PVC in overweight/obese patients. The secondary objective is the comparison of long PVCs and “regular” short PVCs in terms of their ability to administer intravenous therapy through the cannula up to 5 days postoperatively. Tertiary objectives are a portion of long PVCs that are able to ensure blood draw up to 5 days postoperatively, time needed to insert PVC in each group, number of needle tip redirections in both groups, and reinsertion of PVC needed in both groups for any reason.

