### Outcomes {12}

In order to achieve primary and secondary outcomes, the number of attempts, number of cannulas used, tip redirections, time needed to insert the cannula, and proportion of cannulas that requires reinsertion, all this is recorded in the study protocol (Fig. 2) during the procedure. Then researchers will compare both groups to each other. These outcomes are crucial to determine clinical efficacy not just on insertion, but to compare the service life of the cannula inserted. The lifespan of the cannula is related to site of insertion (flexion point), damage to the vessel wall (number of redirections, 1^st^ pass), and proportion of cannula width to vessel diameter. Risks of peripheral vein cannulation are well known and, in general, considered minor.

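### The secondary endpoint is counted per cannula rather than per randomised patient, and the text does not say whether replacement cannulas enter the rate

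*Protocol article*

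**What the plan says.** Statistical methods {20a} defines the secondary endpoint twice. The first definition is that the "failure rate is defined as the proportion of cannulas requiring reinsertion within 5 days after insertion". Later in the same paragraph, "the failure rate is calculated from the ratio of cannulas that did not fail to cannulas that failed for any reason in each group", this time over the first five days after surgery. On the test, "The primary and secondary outcomes will be evaluated using the" χ² test, applied to differences between groups.

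The abstract gives the endpoint without naming a device: "The secondary endpoint is a failure rate of the peripheral venous cannula to administer intravenous therapy up to 5 days postoperatively". Objectives {7} words it by device: "The secondary objective is the comparison of long PVCs and “regular” short PVCs in terms of their ability to administer intravenous therapy".

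Outcomes {12} lists among the recorded items "the number of attempts, number of cannulas used, tip redirections, time needed to insert the cannula, and proportion of cannulas that requires reinsertion". Intervention description {11a} provides the ultrasound-experienced physician for the preoperative insertion in the block room. No section says by which technique, or with which device, a later replacement is placed.

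For difficult insertions, {11b} states: "The method should be discontinued after two unsuccessful attempts and another experienced practitioner should be sought". If no such practitioner is available, the case is recorded as a failure.

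**The concern.** The unit randomised is the patient, while the unit in the endpoint's numerator and denominator is the cannula. The two coincide only if each patient contributes exactly one cannula, and the article does not say so. It lists reinsertion and the number of cannulas used as outcomes, so more than one cannula per patient is foreseen.

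Two things follow if every cannula counts. First, cannulas in the same patient share the same veins, so their failures are likely to be correlated. The χ² test treats them as independent, and patients with poor veins contribute the most units. Second, a replacement counts in the allocated group's rate however it was placed, so the rate no longer describes only the randomised insertion.

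The wording also leaves open what is being compared (device or group), which summary is meant (a proportion or a ratio of non-failed to failed) and when the five days begin (insertion or surgery).

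**Working it through.** **The plan's own figure.** The article gives no numerical assumption for the secondary endpoint. Its 162 patients rest on failure of the first insertion, 20% against 5%. A one-sided 5% test with 90% power gives 82 per arm, or 164, close to 162; a two-sided test gives 202. Neither bears on this point.

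**Inputs.**
- From the article: 200 patients, taken as 100 per arm (1:1 is assumed); an upper cannula failure rate of 63%, quoted under {6b} for poorly sited cannulas; the χ² test.
- Assumed: failure rates of 20% and 40%; within-patient correlation ρ of 0, 0.1, 0.3 and 0.5; at most four cannulas per patient; each failed cannula replaced.

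**Step 1: false-positive rate with no true difference.** Each patient has a failure risk drawn from a Beta distribution with mean μ and parameters a = μ(1−ρ)/ρ and b = (1−μ)(1−ρ)/ρ. At ρ = 0 the risk is μ for everyone. With f failures among c cannulas in each arm, and p̄ the pooled rate, the test rejects when |f₁/c₁ − f₂/c₂| / √[p̄(1−p̄)(1/c₁ + 1/c₂)] > 1.96. Rejection rates over 10,000 simulated trials, counting every cannula:

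| First-cannula failure | ρ = 0 | ρ = 0.1 | ρ = 0.3 | ρ = 0.5 |
|---|---|---|---|---|
| 20% | 4.8% | 8.4% | 13.9% | 17.7% |
| 40% | 4.9% | 7.4% | 9.9% | 12.9% |
| 63% | 4.9% | 6.4% | 7.8% | 8.7% |

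Counting only each patient's first cannula, the rejection rate is 4.7–5.7% in every setting. A separate simulation with mean failure of 30–50% and a cap of three or four cannulas gave 6.4–7.9% at ρ = 0.1 and 9.0–12.1% at ρ = 0.3.

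The rate itself also shifts. At 40% and ρ = 0.3, the 100 patients in an arm supply about 179 cannulas, of which 50.6% fail, because the patients at highest risk supply the most units.

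**Step 2: effect of replacements on the risk ratio.** Assume first cannulas fail in 40% (Group C) and 20% (Group USG), so the first-cannula risk ratio is 0.20/0.40 = 0.50. Assume also that every replacement in either group is palpated and fails at 40%. Group C stays at 40% per cannula. For Group USG:

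- At most two cannulas: (0.20 + 0.20×0.40)/(1 + 0.20) = 0.28/1.20 = 0.233, risk ratio 0.58.
- At most four: (0.20 + 0.08 + 0.032 + 0.0128)/(1 + 0.20 + 0.08 + 0.032) = 0.3248/1.312 = 0.248, risk ratio 0.62.
- No limit: 0.333/1.333 = 0.25, risk ratio 0.625.

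**Step 3: proportion against ratio.** The second definition in {20a} is (1−p)/p. A failure proportion of 20% then reads as 0.80/0.20 = 4.0, and 40% as 0.60/0.40 = 1.5. The two definitions are on different scales and run in opposite directions.

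**Step 4: the wordings side by side.** {7} compares long with short cannulas; {20a} calculates the rate in each group; the abstract defines the groups by insertion technique. {20a} counts five days from insertion in one sentence and from surgery in another. For a cannula placed on the day of surgery the two clocks nearly coincide; for a replacement placed later they do not.

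**The case against.** The best defence is that the endpoint was meant for the index cannula only. {11c} calls the intervention a single event that is not repeated. {12} speaks of the service life of the cannula inserted and says its items are recorded during the procedure. Under {18b}, follow-up ends at five days or discharge, so a late replacement could not be observed for five days from its own insertion. Reinsertion may simply be the event, not the start of a new unit. The record form (Fig. 2) is not shown and may settle it. On this reading cannula and patient are the same unit, the χ² test is valid, and Steps 1 and 2 fall away.

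That reading is possible, but the text does not fix it. {11c} concerns adherence, not the denominator, and both definitions in {20a} speak of cannulas without limiting them to the first. Even on this reading, a patient with no successful placement has no clear place in a denominator of cannulas.

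Two stronger inferences are not supported. A reader might infer from {11b} that patients cross to the other technique after two failed attempts; it names another practitioner, not another technique or device. A reader might also infer from {7} that the analysis regroups patients by device and so breaks the randomisation. {20a} analyses by group, and the Discussion ties each device to an arm, so long and short may be shorthand for the arms. This is an inconsistency in wording, not a planned device-based analysis.

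It is also fair that the correlations, the cap on cannulas, the 20% and 40% failure rates and palpated replacement are all assumptions.

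**Conclusion.** The point stands as a defect of definition in a named secondary endpoint. Read literally, {20a} tests cannulas as independent units although patients are randomised. Conditional on a within-patient correlation of 0.1–0.3, and on every cannula counting, the false-positive rate is about 6–14% instead of 5%. It is about 5% at zero correlation or with one result per patient.

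If replacements were palpated and failed at 40%, a first-cannula risk ratio of 0.50 would read as about 0.58–0.63, which understates a benefit of ultrasound. The two effects differ in kind, one on the test and one on the estimate, so no net direction of error is shown. The primary endpoint is not affected. The correction should be made, because it is cheap and removes the dependence on which reading was intended.

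**What to change.** In {20a}, define the secondary endpoint as one yes/no result per randomised patient: failure, for any reason, of the first cannula placed at the study insertion, analysed in the allocated group. In addition:

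- State that patients with no successful study placement count as failures, or give another explicit rule.
- Use the proportion throughout and delete the ratio of non-failed to failed.
- Choose one time origin, insertion or surgery, and use it in every section.
- Reword {7} as Group USG against Group C.
- Report replacement cannulas descriptively, as number per patient.
- Optionally, report the descriptive blood-draw proportion also with all patients allocated to Group USG as the denominator.

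The cost is wording only: reinsertion and the number of cannulas used are already listed as recorded, and clinical care does not change. The downsides are that later cannulas leave the main test and that, if unsuccessful placements count as failures, the endpoint combines insertion success with durability. With the wider denominator, the blood-draw percentage could be somewhat lower.
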